**1. Introduction**

The use of plant protection products (PPPs) will continue to play a significant role in modern agriculture, significantly boosting productivity and allowing farmers to meet increasing global food demands (Damalas, 2009). However, while pesticides offer undeniable benefits, their misuse will remain a significant global public health concern, particularly in low- and middle-income countries (LMICs), where regulatory oversight is often limited (Abou Zeid et al., 2020; Handford et al., 2015). In Lebanon, agriculture is central to rural livelihoods. However, there is insufficient standardized training on pesticide safety, leading to widespread misuse and exposing the environment and human health to significant risks (Abou Zeid et al., 2020; Maddah et al., 2020).

Pesticide exposure has been linked to both acute and chronic health impacts, ranging from immediate symptoms like dizziness and nausea to long-term conditions such as cancer and neurological disorders (Mostafalou & Abdollahi, 2017; Nicolopoulou-Stamati et al., 2016). Despite these well-known risks, many farmers in rural Lebanon will continue to misuse pesticides due to insufficient knowledge about safe handling practices and inadequate access to formal education programs (Maddah et al., 2020). Moreover, the environmental consequences of pesticide misuse, such as water, soil, and air contamination, will continue to pose serious ecological risks (Gevao et al., 2022; Syafrudin et al., 2021; Tsai, 2013). Therefore, addressing this issue through effective educational interventions will be crucial for improving safety practices in farming communities.

Pesticide labels are the primary means manufacturers communicate crucial safety information to users, especially in LMICs (World Health Organization, 2022). However, the effectiveness of these labels will often be compromised by literacy challenges and a lack of understanding of the symbols and color codes they employ. For example, in Lebanon's rural regions like Akkar, where literacy rates are low, farmers will struggle to interpret these labels, thus elevating the risk of unsafe practices (Abou Ibrahim et al., 2023; Waichman et al., 2007). To bridge this knowledge gap, accessible and scalable educational methods, such as video-based interventions, will need to be implemented.

This study will evaluate the effectiveness of a WhatsApp-delivered educational video compared to traditional in-person educational session in improving pesticide label interpretation and safety practices among farmers in Akkar Governorate, Lebanon. Using widely accessible platforms like WhatsApp will allow disseminating important safety information to a larger audience with fewer resources. By leveraging the widespread use of digital technology in the region, this approach aims to provide a scalable solution to reach geographically dispersed and resource-limited farming communities (MHEIDLY et al., 2021). We hypothesize that the WhatsApp-delivered video will be as effective as traditional in-person education in improving farmers’ pesticide handling practices, knowledge, and understanding of label pictograms and color codes.

This study will fill a critical gap in the literature on educational interventions for pesticide safety in LMICs, particularly in Lebanon, where there have been limited studies on innovative training methods for farmers (Maddah et al., 2020; Mardigian et al., 2021). The findings will provide valuable insights into developing effective, resource-efficient interventions to improve pesticide safety, thus promoting both human health and environmental protection in farming communities.

**Hypothesis**

We hypothesize that a WhatsApp-delivered educational video will be as effective as a traditional in-person educational session in enhancing farmers' pesticide safety knowledge, practices, and interpretation of pictograms and color codes on pesticide labels.

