**Study Objectives**

- **Primary Objective**: To assess the effectiveness of a WhatsApp-delivered educational video compared to a traditional in-person educational session in improving the interpretation of pesticide labels and safety practices among farmers in Akkar Governorate, Lebanon.
- **Secondary Objective**: To determine if the WhatsApp-delivered video improves the use of personal protective equipment (PPE) and safe pesticide-handling practices.

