   The participants in this group will receive a 4-minute educational video on pesticide safety distributed via WhatsApp. The video will cover essential topics on pesticide use, focusing on reading pesticide labels, understanding FAO pictograms, interpreting color codes, and practicing safe handling procedures, including using personal protective equipment (PPE). Visual aids and examples will be incorporated into the video to enhance comprehension, and the content will be presented in Arabic to ensure clarity and accessibility. The video will be available for rewatching, allowing flexible, self-paced learning. Participants in this group will receive a transportation fee as an incentive for participating.
3. **Traditional Educational Session Group (TESG)**
   Participants in the traditional educational session group will attend an in-person, interactive training session. This session, led by the primary researcher with support from a plant protection specialist and an environmental health professor, will use PowerPoint presentations and encourage group discussions. Topics covered will mirror those in the video, including pesticide safety, label interpretation, pictograms, color coding, and PPE usage. The face-to-face format will allow for immediate questions, personalized guidance, and opportunities for farmers to share their experiences. The session will take place in the Safadi Foundation’s conference room in Der Dalloum, Akkar, with participants receiving transportation fees and breakfast as incentives.

Each intervention is designed to improve the participants' knowledge, practices, and interpretation of pesticide safety labels, with the goal of assessing which format—digital or traditional—is more effective in a resource-limited setting. The interventions are specifically crafted to address language and literacy barriers, ensuring accessible and practical education for the farmers involved.

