**12. Statistical Analysis**

The statistical analysis for this study will be conducted using the Statistical Package for the Social Sciences (SPSS; Chicago, IL, USA), version 25, with statistical significance set at p<0.05p < 0.05p<0.05.

Descriptive Analysis

The baseline characteristics of the participants across the three groups—Control Group (CG), Digital Video-Based Learning Group (DVBLG), and Traditional Educational Session Group (TESG)—will be summarized using descriptive statistics. For continuous variables, such as age and years of experience, we will calculate the mean and standard deviation (SD). For categorical variables, such as gender and prior pesticide training, frequencies and percentages will be presented.

Baseline Comparison

To confirm the comparability of the groups before the intervention, baseline characteristics will be assessed using a one-way analysis of variance (ANOVA) across the three groups, ensuring no significant differences could affect outcome interpretation.

Primary Outcome Analysis (Per-Protocol)

A per-protocol approach will be applied to analyze the primary outcomes, which include knowledge of pesticide safety, interpretation of pesticide labels, and understanding of the environmental impacts of pesticide misuse. The analysis will proceed as follows:

- Within-Group Changes: Paired t-tests will assess changes from baseline to post-intervention for each group.
- Between-Group Differences: A one-way ANOVA will compare differences between the groups in post-intervention scores. If significant differences are detected, post hoc tests (e.g., Tukey’s HSD) will be conducted to explore pairwise comparisons between groups.

Secondary Outcome Analysis

For secondary outcomes, including PPE usage and pesticide-handling practices, changes within each group will be assessed using paired t-tests, while differences between groups will be analyzed using one-way ANOVA with post hoc tests for further analysis as needed.

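### The hypothesis is that the video equals the in-person session, but the planned between-arm tests can only refute equality, not support it

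*Protocol*

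**What the plan says.** The Hypothesis section reads "We hypothesize that a WhatsApp-delivered educational video will be as effective as a traditional in-person educational session". The Introduction says the same: "We hypothesize that the WhatsApp-delivered video will be as effective as traditional in-person education". The primary objective concerns the same two arms but is neutral on direction: "To assess the effectiveness of a WhatsApp-delivered educational video compared to a traditional in-person educational session". Section 7 (Description of the interventions) closes with a different aim, "with the goal of assessing which format—digital or traditional—is more effective in a resource-limited setting".

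For the primary outcomes, Section 12 (Statistical Analysis) says "A one-way ANOVA will compare differences between the groups in post-intervention scores". Pairwise comparisons are conditional: "If significant differences are detected, post hoc tests" follow, with Tukey's HSD as the example. For secondary outcomes, "differences between groups will be analyzed using one-way ANOVA with post hoc tests for further analysis as needed". The only other tests are paired t-tests within each arm, which do not compare arms. The Protocol gives no equivalence or non-inferiority margin and no confidence-interval criterion. Section 6 sizes the trial on a rise in label reading from 4% to 29%, not on a video-versus-session difference.

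**The concern.** Equal effectiveness is an equivalence or non-inferiority claim. It needs a stated margin, and data that exclude a deficit larger than that margin. ANOVA and Tukey's HSD take equality as the null hypothesis. A significant video-versus-session result counts against the stated hypothesis; a non-significant one leaves the matter open. No outcome of the planned between-arm tests supports the hypothesis as worded.

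The case for a low-cost, scalable WhatsApp format depends largely on how the video compares with the session. If the report follows the hypothesis as worded, the only between-arm result that could be offered in its favour is a failure to reject. At these sample sizes that happens often even when the video is moderately worse. Section 7 adds to the problem: a reader cannot tell whether the trial sets out to show that the formats are equal or to find the better one.

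**Working it through.** **1. The plan's own sample size.** Inputs from Section 6: 4% versus 29%, alpha 0.05, power 80%. Two-sided, pooled variance under the null, mean rate 0.165:

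n = [1.96·√(2·0.165·0.835) + 0.842·√(0.04·0.96 + 0.29·0.71)]² / 0.25² = 33.4, so 34 per arm.

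This agrees with the stated figure of approximately 35, at which power is 81.9%. The sample size is sound for 4% versus 29%, but it does not address video versus session.

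**2. Arm sizes.** The Protocol gives three totals: 105 (Section 6), 133 (Section 5, after the exclusion criteria) and 150 (Section 5, recruitment). Divided by three, these are 35, about 44 and 50 per arm.

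**3. How often a real deficit gives a non-significant Tukey comparison.** Assumptions: a roughly normal score, common SD, no dropouts, true video deficit d in SD units. The test statistic is non-central t with df = 3(n − 1) and non-centrality d·√(n/2). The critical value is q/√2, with q the 5% studentized range point for three groups.

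| | 35 per arm | 44 per arm | 50 per arm |
|---|---|---|---|
| df | 102 | 129 | 147 |
| Critical value q/√2 | 2.378 | 2.371 | 2.368 |
| Non-centrality, d = 0.4 | 1.673 | 1.876 | 2.000 |
| P(non-significant), d = 0.4 | 75.5% | 68.6% | 64.1% |
| Non-centrality, d = 0.5 | 2.092 | 2.345 | 2.500 |
| P(non-significant), d = 0.5 | 60.9% | 50.8% | 44.6% |
| P(non-significant), d = 0.6 | 44.6% | 32.9% | 26.4% |
| P(non-significant), d = 0.8 | 16.8% | 8.5% | 5.3% |

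The half-width of the Tukey 95% interval, (q/√2)·√(2/n), is 0.57, 0.51 and 0.47 SD.

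**4. The two-stage procedure as written.** A simulation of 100,000 trials required a significant ANOVA before Tukey, with the session assumed 1 SD above control and the video 0.5 SD below the session. The video-versus-session difference was found in 39.0% (35 per arm) and 49.2% (44 per arm) of trials, so it was missed in 61.0% and 50.8%. The ANOVA step changes nothing material here.

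**5. What a non-inferiority claim would need.** Assume true equality, a one-sided 2.5% level (lower limit of an unadjusted 95% interval), 80% power and no baseline adjustment. The smallest margin is (1.96 + 0.842)·√(2/n): 0.67 SD at 35, 0.60 SD at 44 and 0.56 SD at 50 per arm. Conversely, n = 2(1.96 + 0.842)²/margin² gives 63, 99, 175 and 393 per arm for margins of 0.5, 0.4, 0.3 and 0.2 SD.

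**The case against.** **The misuse is inferred.** A reader might conclude that the plan will declare the formats equal when p exceeds 0.05. The Protocol nowhere says so: Section 12 lists tests and gives no rule for interpreting a non-significant result. This stands. The supportable point is that the planned tests cannot support the stated hypothesis.

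**A clearly worse video would not usually go undetected.** A reader might infer that it would. That holds at 0.4 SD. At 0.5 SD with 44 per arm it is about even, and at larger deficits it is false (32.9% at 0.6 SD and 8.5% at 0.8 SD, 44 per arm). Without a score SD, the Protocol cannot settle which deficit counts as clearly worse.

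**The 4%-to-29% behaviour is not a listed outcome.** It is tempting to restate the problem in those rates, for example a video giving half the gain. Reading labels before mixing is the sizing basis only. Section 10 lists pictogram interpretation, health-risk knowledge and environmental understanding as primary, and Section 12 compares scores. Such figures would not describe a primary outcome.

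**The control arm gives some protection.** A very noisy trial would also fail to separate either format from no intervention, so noise alone would not make the hypothesis look confirmed. This limits the problem, but separating both formats from control does not show that they are equal to each other.

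**Comparing formats two-sidedly suits the objective and Section 7.** It does, so the hypothesis wording is what is out of line. A statistical analysis plan not seen here might add an interval rule or a margin. The Protocol itself, however, states the hypothesis, names the tests and sets the sample size on another contrast.

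**Conclusion.** The point holds as a mismatch between hypothesis and analysis. The Introduction and the Hypothesis section claim equal effectiveness, Section 12 fixes only tests whose null is equality, and Section 7 states a third framing. A non-significant video-versus-session result would be weak support: under assumed deficits of 0.4 to 0.5 SD it occurs in 44.6% to 75.5% of trials across the three stated sample sizes. These figures rest on normal scores, a common SD and full retention. Losses under the per-protocol approach and list-wise deletion would raise them. The mismatch itself does not depend on the assumed deficits.

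**What to change.** 1. In the Introduction and the Hypothesis section, reword the hypothesis to superiority of each active arm over control.
2. In Section 12, report the video-minus-session difference on each primary score with its 95% confidence interval, so that the primary objective is answered by an estimate. State that a non-significant ANOVA or post hoc test will not be read as equal effectiveness.
3. Align the aim at the end of Section 7 with the reworded hypothesis.
4. Keep an equal-effectiveness claim only if a non-inferiority margin is justified by the loss of benefit that would be acceptable, and the confidence interval for video minus session lies above it. The margin must not be derived from the sample size: 44 per arm gives 80% power only for about 0.60 SD under true equality, which is wider than the 0.4 to 0.5 SD deficits examined above. A tighter margin would need the larger arms shown in the working.

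Steps 1 to 3 cost some wording and one reported interval, with no new data or participants. The downside is that the trial may be unable to claim that the video is as effective as the session.

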**Study Objectives**

- **Primary Objective**: To assess the effectiveness of a WhatsApp-delivered educational video compared to a traditional in-person educational session in improving the interpretation of pesticide labels and safety practices among farmers in Akkar Governorate, Lebanon.
- **Secondary Objective**: To determine if the WhatsApp-delivered video improves the use of personal protective equipment (PPE) and safe pesticide-handling practices.

**Ethical Considerations**

This study will be conducted following ethical guidelines, with approval sought from the Institutional Review Board (IRB) of The Doctoral School of Science and Technology at the Lebanese University. The study will not commence until IRB approval is granted, and participants will be fully informed about the study's objectives, procedures, and their rights.

**4. Study Design**

This will be a parallel-group, three-arm, randomized controlled trial (RCT) designed to evaluate the impact of two educational interventions on farmers' knowledge and practices related to pesticide use. Similar content will be used in both the educational video and the educational session.

**Study Arms**:

1. **Control Group (CG)**: Farmers will receive no intervention.
2. **Traditional Educational Session Group (TESG)**: Farmers will attend an in-person educational session on pesticide safety, health impacts, and label interpretation.
3. **Digital Video-Based Learning Group (DVBLG)**: Farmers will receive a 4-minute educational video via WhatsApp containing the same content as the in-person session.

**Randomization**

Participants will be randomly assigned to one of three groups: the Control Group, the Digital Video-Based Learning Group (DVBLG), and the Traditional Educational Session Group (TESG). Each participant’s phone number will serve as their unique identifier, simplifying group allocation and follow-up communication without requiring participants to remember a specific code. To ensure a random allocation, we will use the RAND function in Microsoft Excel.

The process will be as follows:

1. Each participant’s phone number will be entered in a single column in Excel. The RAND function will generate a random number for each participant. These random numbers will then be used to sort the list of participants in ascending order, resulting in a randomized list.
2. Based on this sorted list, participants will be allocated sequentially to each of the three groups, ensuring equal distribution.
3. To facilitate communication, we will create a WhatsApp group for each team. We will use the group to invite the TESG to the educational session, send the educational video to the DVBLG, and provide them with instructions to watch it. Additionally, we will use the group to call them for the post-assessment.

This approach will ensure a transparent and unbiased randomization process, allowing us to assess intervention effectiveness across comparable groups.

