**Exclusion Criteria**:

- Farmers who do not meet the inclusion criteria.

A total of 133 participants will be enrolled and randomized.

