**Participants recruitment:**

Participants for this study will be recruited from a list of 418 agricultural farmers provided by the municipalities of three nearby coastal villages in the Akkar Governorate, northern Lebanon. These farmers are registered in the municipal database, making them eligible for recruitment in the study due to their involvement in agriculture within this region. Systematic sampling will be used, whereby every third farmer on the list will be contacted to determine eligibility and interest in participating.

To qualify, participants must be at least 18 years old, engaged in agricultural activities within the coastal area, actively using chemical pesticides, and have access to WhatsApp on a personal or family member's device. Farmers meeting these criteria will be informed about the study’s objectives, procedures, and voluntary nature, emphasizing confidentiality and the right to withdraw at any time. Consent will be obtained through signatures or fingerprints, depending on literacy levels. Farmers who are not eligible or choose not to participate will be replaced by the next farmer on the list, and this process will continue until the required sample size of 150 participants is reached.

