**6. Sample Size Calculation**

The sample size calculation for this randomized controlled trial will be based on prior data from a cross-sectional study conducted in the same region, which found that only 4% of farmers routinely read pesticide labels before preparing pesticide mixtures. To achieve a statistically meaningful improvement with our educational intervention, we aim to detect an increase in this behavior by 25%—raising it from 4% to 29%.

Using a significance level of 0.05 and a power of 80%, we estimate that each group (Digital Video-Based Learning Group, Traditional Educational Session Group, and Control Group) will require approximately 35 participants, totaling 105 participants across the three groups. However, we plan to recruit additional participants to account for potential attrition and ensure a robust final sample. The number of these additional participants will be determined based on observed participation and retention rates during the recruitment phase, allowing us to meet our target sample size despite potential dropouts. This approach will help maintain sufficient statistical power throughout the study, even if some participants cannot complete all stages.

7. **Description of the interventions.**

This randomized controlled trial will involve three distinct groups, each receiving different levels of intervention:

1. **Control Group (CG)**
   Participants in the control group will receive no educational intervention and will serve as a baseline to compare the effects of the other interventions. This group will only participate in baseline and follow-up assessments to measure changes in knowledge, practices, and understanding of pesticide labels without external educational support.
2. **Digital Video-Based Learning Group (DVBLG)**

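### Sorting the single batch draw by village and education, and adjusting for both, would cheaply improve balance and precision; the unstratified draw itself is valid

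*Protocol*

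**What the plan says.** **Allocation.** Section 4 of the protocol (Randomization) enters every phone number in one column, sorts once by an Excel random number, and then: "Based on this sorted list, participants will be allocated sequentially to each of the three groups, ensuring equal distribution". It names no stratum, block or minimisation factor. It closes by saying that the method permits assessment across comparable groups.

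**Village and education.** Farmers come from lists "provided by the municipalities of three nearby coastal villages" (Participants recruitment), so village is known at the outset. Education level is collected in the questionnaire (section 8). The Introduction names limited literacy as one barrier to reading labels, alongside poor understanding of symbols and colour codes.

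**Timing.** Section 9 places screening in June and puts consent, baseline data and randomisation together in 1–21 July.

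**Analysis.** Section 12 tests baseline characteristics by one-way ANOVA, "ensuring no significant differences could affect outcome interpretation". It then compares post-intervention scores by one-way ANOVA with Tukey tests and names no covariate.

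**Totals.** Three appear: "A total of 133 participants will be enrolled and randomized" (Exclusion Criteria); "this process will continue until the required sample size of 150 participants is reached" (Participants recruitment); and "will require approximately 35 participants, totaling 105 participants across the three groups" before an unspecified allowance for attrition (section 6).

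**The concern.** When the whole list is compiled before a single draw, stratifying needs little more than extra sort keys. This plan does not use that opportunity. Dealing the arms out equally controls only the number of farmers per arm.

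Education plausibly affects pictogram interpretation, which is a primary outcome. Village may matter as well, for example through travel to the single session venue, although the protocol does not say so. With about 44 farmers per arm, visible chance differences are common. Because the planned comparison is unadjusted, such differences pass straight into the contrasts, including video versus session.

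The baseline ANOVA does not help. A test after randomisation describes imbalance but cannot prevent it. At stake are some precision and how convincing the claim of comparable groups will look in the baseline table.

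**Working it through.** **The plan's own figure.** The protocol states no size or probability of imbalance. Its only relevant figure is the arm size. For 4% versus 29%, two-sided 0.05 (sidedness assumed) and 80% power, with mean proportion 0.165:

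n = [1.96·√(2·0.165·0.835) + 0.842·√(0.04·0.96 + 0.29·0.71)]² / 0.25² = (1.029 + 0.416)² / 0.0625 ≈ 33.4, so 34 per arm.

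This agrees with the stated 35 or so. Dealing out 133 farmers gives arms of 45, 44 and 44.

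**Assumptions, because the documents give no shares.** Villages 33/33/33, 50/30/20 or 70/20/10; low education 30–50%, with 40% as the central value. The 15-point threshold is a convention chosen for this check.

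**One factor, one named pair of arms.** The SD of the difference in a share p is about √(2p(1−p)/n). With p = 0.40 and n = 44 this is √(2·0.24/44) = 0.104, so 15 points is 0.15/0.104 = 1.44 SD, with a two-sided tail of about 15%. The exact hypergeometric figures are 13% (45 v 44) and 16% (44 v 44). A gap of 20 points or more has a chance of about 5–6%.

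**One factor, any pair of arms.** For low education at 40% and N = 133, about 30%. Over prevalences from 10% to 50% the chance runs from 5% to 32%.

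**At least one gap anywhere.** Three village shares plus education, over three pairs of arms, make 12 gaps. Simulated unstratified 1:1:1 draws give these chances of at least one gap of 15 points or more (ranges are for 30–50% low education):

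| Total | Villages equal | 50/30/20 | 70/20/10 |
|---|---|---|---|
| 105 | 75–78% | 73–75% | 61–65% |
| 133 | 70% | 66–67% | 56–57% |
| 150 | 62–64% | 59–63% | 47–52% |

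For the village shares alone at N = 133 the figures are 56%, 52% and 38%. The lowest cell, 47%, needs 30% low education; at 40% that setting gives about 50%.

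**After the change.** At N = 133 with equal villages and 40% low education, sorting by village, education and the random number, with rotation from a random start, cuts the 95th percentile of the largest gap from about 27 to 2 points (village) and from about 24 to 4–5 points (education). No gap of 15 points or more occurred at any of the three totals.

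**Effect on the comparison.** In outcome SD units, the standard error of a two-arm difference is √(2/44) = 0.213. If low education costs an assumed 0.5 SD:

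- A 20-point gap shifts a contrast by 0.20·0.5 = 0.10 SD, or 0.10/0.213 = 0.47 standard errors.
- Education then explains 0.5²·0.4·0.6 = 0.06 of the variance. Adjusting for it moves the standard error to 0.213·√0.94 = 0.207.
- A baseline score with correlation r to the post score scales the standard error by √(1−r²). It gains more than education once r exceeds √0.06 ≈ 0.25.

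**The case against.** Simple randomisation with equal arms is a sound method. The usual standard error already allows for chance imbalance, so the plan neither biases the comparison nor inflates the type I error. Not stratifying is a choice. Section 12's phrase about significant differences describes the purpose of a baseline test; it is not a balance requirement that the draw then fails. All of this stands.

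A reader might infer that an imbalance of 15 points is likely in any factor that matters. The figures do not support that. The high percentages pool 12 gaps. For education between video and session the chance is about 15%, and a 20-point gap there is rarer still. Nor can village be credited with a known effect: the protocol calls the villages nearby, pays session attendees' transport and gives no distances.

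The literacy argument also has limits. Literacy is one barrier among those named, the interventions are designed around it (section 7), and surveyors read the questions aloud (section 8). Stratifying is not wholly free either, since section 9 does not state outright that all baseline data precede the draw.

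These points reduce the size of the gain. They do not remove the case for a change this cheap.

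**Conclusion.** This is an optional improvement, not a flaw that threatens validity. One unstratified draw leaves village and education to chance although one is known and the other is collected, and the protocol's between-arm analysis ignores both.

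Assuming 40% low education and village shares from equal to 70/20/10, at least one gap of 15 points or more somewhere has a chance of about 57–70% at 133 farmers, and about 50–78% over totals of 105 to 150. For education alone it is about 30% over any pair of arms and about 15% for video versus session.

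The documents do not support reading this as bias, as an internal contradiction, or as a probable imbalance in any single factor. The loss is modest: some precision, and the visible comparability that section 4 claims. The size of the effect on outcomes rests on an assumed 0.5 SD education effect; no effect of village can be quantified from the documents.

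**What to change.** In the Randomization section, state that the draw takes place once baseline data are complete for all farmers. Sort the list by village, then education (low/higher, with the cut defined beforehand), then the fixed random number. Assign the three arms in rotation down that list from a randomly chosen starting arm. Say rotation explicitly: giving each arm a consecutive third of a list sorted by village would place whole villages in single arms.

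In section 12, include village and education as factors in the between-arm model, ideally with the baseline score of the same outcome, which section 11 already collects. The factors remain useful after a balanced draw because per-protocol exclusions and list-wise deletion can disturb balance among those analysed. Present the baseline table as description and drop the statement that a test ensures comparability.

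Cost: two sort keys in the same spreadsheet and two or three model terms. Village and education must be on file for every farmer before the draw. The precision gain from education alone is small (standard error about 0.213 to 0.207 SD under the assumption above).
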